**Methods and design:**

Hundred and twenty patients with Parkinson’s disease will be recruited to participate in this multi-centered, single blind, randomized controlled trial. Patients in Hoehn & Yahr stage II-III, with or without freezing of gait, and who report dual task difficulties will be included. All patients will undergo a six-week control period without intervention after which they will be randomized to integrated or consecutive task practice. Training will consist of standardized walking and cognitive exercises delivered at home four times a week during six weeks. Treatment is guided by a physiotherapist twice a week and consists of two sessions of self-practice using an MP3 player. Blinded testers will assess patients before and after the control period, after the intervention period and after a 12-week follow-up period. The primary outcome measure is dual task gait velocity, i.e. walking combined with a novel untrained cognitive task to evaluate the consolidation of learning. Secondary outcomes include several single and dual task gait and cognitive measures, functional outcomes and a quality of life scale. Falling will be recorded as a possible adverse event using a weekly phone call for the entire study period.

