Therefore, the primary aim of this study is to compare the effectiveness of consecutive versus integrated training (tested by combining walking with cognitive exercises) on DT gait performance in PD. We hypothesize that IDT practice will resort in better dual task outcomes and better consolidated learning results, particularly in patients without cognitive impairment. As secondary questions we will examine which dual task training mode is most beneficial in terms of fall risk reduction and leads to the best dual task gains in freezers versus non-freezers. Here, we describe the design of this training study, also referred to as the DUALITY trial.

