### Data analysis/statistics

A statistical analysis plan will be developed prior to unblinding and analysis. The primary data analysis will be performed according to an intention to treat principle. The primary endpoint, the DT walking performance at test session 1, 2, 3 and 4 will be evaluated using a linear mixed model. Tests will be two-sided with α 0.05. The fixed factors will be treatment (IDT vs. CTT), test session (1, 2, 3 and 4) and the interaction between test session and treatment group. Subject will be a random factor. The treatment difference will then be estimated by the appropriate contrast for the difference between the mean scores at test session 1, 2, 3 and 4. Secondary endpoints will be analyzed in a similar way. As a secondary question we will also model the three-way interaction between subgroup, i.e. those with and without freezing of gait (defined as a score of 1 on the New FOGQ), treatment group and time. Fall frequency data will be analyzed using a negative binomial model depending on the distribution of the data.

The influence of center, disease severity (Hoehn and Yahr scores) and cognition will be explored by including the interaction terms between treatment and each of these variables in the model. Throughout, 95% confidence intervals will be determined. Sensitivity analyses will be carried out to evaluate the impact of missing values on the outcome.

In addition descriptive statistics will be presented by means and standard deviations, as appropriate. When data are skewed, medians and quartiles will be calculated and for categorical data, frequencies and percentages will be presented.

Data will be analyzed using the data analysis software package IBM SPSS Statistics (version 19).

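### Effect modification by center, disease severity and cognition is planned as a treatment-by-variable term that averages over two pre-training sessions, a valid but half-diluted, low-power test of the exploratory question

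*Protocol article*

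**What the plan says.** All references are to the Protocol article. Under Data analysis/statistics, "the DT walking performance at test session 1, 2, 3 and 4 will be evaluated using a linear mixed model". The model is set out as follows: "The fixed factors will be treatment (IDT vs. CTT), test session (1, 2, 3 and 4) and the interaction between test session and treatment group", and "Subject will be a random factor". The treatment difference is to be read from a contrast between sessions.

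Two forms of effect modification are then described. For freezing, "we will also model the three-way interaction between subgroup, i.e. those with and without freezing of gait", treatment group and time. For center, Hoehn and Yahr score and cognition, the influence is to be "explored by including the interaction terms between treatment and each of these variables in the model"; session does not appear in that sentence.

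On timing, the Abstract (Methods and design) states: "All patients will undergo a six-week control period without intervention after which they will be randomized to integrated or consecutive task practice". Testing takes place before and after that control period, after training and at follow-up. On purpose, the Background expects integrated training to give "better consolidated learning results, particularly in patients without cognitive impairment".

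**The concern.** In a model that takes all four sessions as outcomes, the treatment main effect is not the training effect. The training effect is the change in the arm difference from the pre-training to the post-training sessions, that is, a treatment-by-session contrast. A variable that modifies it does so through treatment by session by variable. The protocol uses that form for freezing but not, as worded, for the other three variables.

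A treatment-by-variable term without session is constant over the four sessions. It compares arm differences in the four-session average across levels of the variable, and half of that average was measured when no training effect could exist.

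What is at stake is mainly cognition, because the hypothesis predicts a larger advantage of integrated training in patients without cognitive impairment. The reported estimate would be too small by design, and a non-significant result would carry little information. Randomisation is stratified by freezing and Hoehn and Yahr stage but not by cognition, so chance pre-training differences between arm-by-cognition cells enter this term directly.

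**Working it through.** **Inputs from the protocol (Sample size; Data analysis/statistics).** Mean dual task gait speed 0.77 m/s, SD s = 0.21, assumed arm difference 15%, total 108 before loss to follow-up (54 per arm if split equally), two-sided alpha 0.05.

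**Inputs assumed here.** Equal correlation rho between any two sessions (compound symmetry), a binary modifier splitting each arm 50/50, complete data, and a modification D of the training effect that is equal at sessions 3 and 4. For illustration D = 0.15 × 0.77 = 0.1155 m/s, as large as the whole assumed treatment effect.

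**The plan's own figure.** n per arm = 2 × (1.96 + 0.84)² × 0.21² / 0.1155², which rounds up to 52. The noncentral t version gives 53 (106 in total), and 54 per arm has 80.8% power. The stated 108 is therefore consistent with these inputs. The protocol gives no power figure for any interaction.

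**What the term estimates.** Treatment by variable, constant over sessions: (0 + 0 + D + D)/4 = D/2 = 0.0578 m/s. This does not depend on rho or s. If the modification appeared only at follow-up, it would be D/4. Treatment by variable by (mean of sessions 3 and 4 minus mean of sessions 1 and 2): D = 0.1155 m/s.

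**Precision.**
- SD of a subject's four-session mean: s × √((1 + 3rho)/4).
- SD of a subject's post-minus-pre difference: s × √(1 − rho).
- SE of the interaction in either case: 2 × SD × √(2/54).

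At rho = 0.7:
- Two-way: SD = 0.21 × √0.775 = 0.185; SE = 0.0712; z = 0.0578/0.0712 = 0.81.
- Three-way: SD = 0.21 × √0.3 = 0.115; SE = 0.0443; z = 0.1155/0.0443 = 2.61.

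| rho | Two-way SE | Two-way power | Three-way SE | Three-way power |
|---|---|---|---|---|
| 0.5 | 0.0639 | 14.8% | 0.0572 | 52.4% |
| 0.7 | 0.0712 | 12.8% | 0.0443 | 74.2% |
| 0.8 | 0.0745 | 12.1% | 0.0361 | 89.2% |
| 0.9 | 0.0777 | 11.5% | 0.0256 | 99.5% |

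The ratio of the two z values is √((1 + 3rho)/(1 − rho)): 2.2 at rho 0.5, 3.2 at 0.7 and 4.1 at 0.8. It exceeds 1 for any positive rho and does not depend on D or s. With D halved to 0.0578 at rho 0.7, z is 0.41 against 1.30, so power is about 7% against 26%.

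**Check by simulation** (mixed model with random subject intercept, rho 0.7, 108 patients, 200 runs per scenario):
- True D = 0.1155: the mean two-way estimate was 0.060 and the mean three-way estimate 0.114; rejection rates were 17% and 75%.
- No difference anywhere: rejection rates 3% and 5%.
- An arm-by-subgroup difference of 0.1155 m/s imposed equally at all four sessions, with no difference in training effect: rejection rates 43% and 4%. This shows how the two-way term responds to a given baseline imbalance. It is not an average error rate under randomisation.

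**The case against.** The strongest reply concerns reading. The sentence is condensed, does not call the terms two-way and does not exclude session. A statistical analysis plan is promised before unblinding and could cross each variable with treatment wherever treatment enters the model. This reading is possible. However, the preceding paragraph names the three-way form explicitly for freezing, and the contrast favours the literal reading. The protocol commits to a term here, so this is more than an omitted detail.

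A reader might also infer that the two-way term does not test effect modification at all, or that it inflates false positives. The protocol does not support this. Randomisation makes the expected arm-by-variable difference at sessions 1 and 2 zero, so the term is non-zero in expectation only if the training effect differs. Chance imbalance is already in its standard error, and the simulated rejection rate with no difference was 3%. The defect is dilution and lost power.

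It is also fair to say that these analyses are labelled exploratory, that center and severity carry no stated hypothesis, and that 95% confidence intervals are promised throughout, which would show imprecision. The last point helps only in part, because the interval would be centred on half the relevant quantity. Finally, the power figures rest on assumed values, and at rho 0.5 even the three-way contrast reaches only 52%.

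**Conclusion.** The point holds at moderate weight. As worded, the exploratory terms for center, Hoehn and Yahr stage and cognition do not match the contrast that defines the training effect, nor the form planned for freezing. They remain valid tests, but with complete data they recover half of a modification shared by sessions 3 and 4, carry the full between-subject variance and absorb chance baseline differences.

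The halving follows from the design, given equal modification at both post-training sessions. The size of the power loss depends on the assumed correlation, subgroup split and D; the direction does not, for any positive correlation.

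It would be wrong to infer that the primary result is compromised: the primary estimate, its test and the sample size are unaffected. The consequence is confined to subgroup conclusions, and matters most for cognition because the hypothesis names it.

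**What to change.** Replace the sentence with one along these lines: effect modification by center, Hoehn and Yahr stage and cognition will each be explored with the treatment by session by variable interaction, including all lower-order terms, and evaluated at the same between-session contrast as the primary analysis. State that the cognitive score is one measured before randomisation. The protocol does not say which measure is meant, and the outcome table lists some taken only at baseline (MMSE, MoCA, FAB) and some repeated at all four sessions (Scopa-Cog, alternating fluency).

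The cost is one sentence, no new data and a few more terms in each exploratory model. It should be settled in the statistical analysis plan before unblinding. Even so, power for a modest modification will remain limited, and the results should be reported as estimates with intervals.

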## Discussion

Acknowledging that dual tasking forms an integral part of daily functioning, the DUALITY study proposed here aims to investigate the efficacy and safety of a rehabilitation intervention to improve dual tasking in PD patients. We will establish robust evidence on which training modality, i.e. integrated or consecutive training, leads to the best training results and how this compares with a control period without intervention. Given the reduced capacity for consolidation of motor learning in PD [49,73] and the presence of executive deficits [28], it will be established whether dual task learning effects transfer to improvements in daily life and are sustained for 12 weeks without training.

A paucity of dual task studies have been performed in PD patients, most of which with poor methodological designs. This pilot work has shown short-term positive effects on gait performance [42-45], although there was considerable variation in the population, training period and tasks (motor, cognitive) that were studied. This is the first power-based and randomized trial that compares two interventions in an early to mid-stage PD population that are both aimed at improving dual task performance but with contrasting treatment strategies. In analogy with a DT training study in balance-impaired older people [51,52], we expect that both groups will show some improvement on DT outcomes However, as integrated DT training is more cognitively challenging we hypothesize that this will result in a better consolidation and retention of the training effects in line with motor learning theory [74]. In addition, we expect that integrated training will resort in better DT outcomes as the exact practice conditions mimics real life tasks more closely and this is important for transfer of learning [74]. In this study, the evaluation of motor performance will be supplemented by assessment of cognitive performance which allows monitoring of learning effects in both motor and cognitive domains. We focus on assessing various components of executive functions, an area that is specifically shown to be affected in PD patients [28]. This implies that this trial will also provide novel evidence on the impact of cognitive training on executive function in PD which may inform future power-based studies in this area.

This will be the first dual task training study that will look at differences in dual task gains between freezers versus non-freezers after stratification for these subgroups. The results of this study will establish which training strategy is optimal in each subgroup, taking their different cognitive profiles into account. Since freezers show greater executive deficits than their non-freezing counterparts [31-33,75] and learn less well in dual task conditions [34], we anticipate that freezers may benefit more from consecutive training in order to achieve dual task learning.

In conclusion, in this DUALITY trial we will study two different strategies aimed at improving dual tasking in PD patients. We expect that the trial will provide novel and clinically important information on the most effective and safe training strategy in different patient subgroups and in this way will contribute to developing future directions for rehabilitation targets in PD.

### Consent

Written informed consent will be obtained from every patient included in the study. A copy of the written consent will be available for review by the Editor of this journal.

## Abbreviations

PD: Parkinson’s disease; FOG: Freezing of gait; DT: Dual task; CTT: Consecutive task training; IDT: Integrated dual task training; RUMC: Radboud University Medical Centre; MMSE: Mini mental status examination; DBS: Deep brain stimulation; SD: Standard deviation; MoCA: Montreal cognitive assessment; FAB: Frontal assessment battery; UPDRS: Unified Parkinson’s disease rating scale; New FOGQ: New freezing of gait questionnaire; ABC: Activities specific balance confidence scale; ScopaCog: Scales for outcomes of Parkinson’s disease - cognition; ANT: Alternating names test; AIT: Alternating intake test; PDQ-39: Parkinson’s disease questionnaire for quality of life; ADL: Activities of daily living; MPT: Mobile phone task.
